
# OBJECTIVES/AIMS

The goal of this research is to advance the science of multilevel mental health interventions that aim to reduce the disparate, adverse mental health, behavioral, and socioeconomic consequences of the COVID-19 pandemic that are a result of complex interactions between underlying structural inequities and numerous barriers to health care. This community-based participatory research study builds on a long-standing collaboration with 5 community-based organizations (CBOs) and employs a longitudinal waitlist control group design with 5 time points over 32 months. A random probability sample of 1000 Latinx immigrants (RS) will be compared with 240 Latinx immigrants and 60 African refugees recruited through CBOs and randomly assigned to an efficacious peer advocacy and learning model (RIWP; n=150) or a treatment-as-usual waitlist control group (TAU; n=150). This innovative design allows for testing of three nested levels of intervention: 1) peer intervention model; 2) engagement with CBOs; and 3) structural interventions expected in response to the pandemic (e.g., state relief for mixed status families and expanded health insurance coverage), to which all 1300 participants would potentially be exposed. We propose three primary aims to advance mental health intervention and disparities research:

**Aim 1.** Test the effects of the RIWP intervention to reduce adverse consequences of the COVID-19 pandemic for Latinx and Black immigrants and refugees.

**1.1** *Primary Outcomes:* RIWP participants will have decreased psychological distress, daily stressors, and economic precarity as compared to randomly assigned treatment-as-usual waitlist control group (TAU).

**1.2** *Secondary Outcomes:* RIWP participants will have increased protective factors (social support, access to resources, English proficiency, cultural connectedness, health services use).

**Aim 2.** Test the effects of engagement with CBOs to reduce adverse consequences of the COVID-19 pandemic for Latinx and Black immigrants and refugees.

**2.1** *Primary Outcomes:* CBO participants will have decreased psychological distress, daily stressors, and economic precarity as compared to the comparison group of randomly sampled immigrants (RS).

**2.2** *Secondary Outcomes:* CBO participants will have increased protective factors (social support, access to resources, English proficiency, cultural connectedness, health services use).

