**Aim 3.** Test the effects of RIWP and engagement with CBOs to increase access to benefits of structural interventions (local/state relief-related policies). For this aim, the outcome will be a binary indicator for whether each participant accessed the structural interventions which are implemented. The analyses will be similar to Aim 2, but will use a logit link and consequently drop the e_tij_ term. As mentioned above, while this is written to assume linear changes, we have proposed a process for selecting the longitudinal model to be used with data from the comparison sample and using statistical simulations to evaluate power of the different alternatives.

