**Secondary Aims.** (a)   Examine mechanisms of intervention effectiveness. This secondary aim will be examined through structural equation modeling (SEM) to provide tests of mediation effects through which outcomes are impacted by hypothesized mechanisms. The same models for changes in outcomes which are developed on the random sample^110^ will be used in these analyses. These analyses assess whether differences in outcomes between treatment groups are due to changes observed in protective factors from baseline to post-intervention.^111^ Significant indirect effects are anticipated linking the RIWP intervention with lower follow-up levels of distress, stressors, and economic precarity, via pre-to post-intervention increases in protective factors. Bootstrapped standard errors^105^ will be used to derive confidence intervals for these mediated effects; standard errors will be adjusted for clustering of participants within CBOs using sandwich estimators.^106^ (b) Explore whether race/ ethnicity, biological sex, gender identity, sexual orientation, age, and SES moderate intervention impact. For this secondary aim, stratification variables will be incorporated as level 2 covariates in the models described above. Moderation will be assessed via interactions between the multiple levels of treatment and each of these moderators.^107^ (c) Track local/state policy changes to obtain preliminary estimates of effects of these structural interventions on mental health, stressors, and economic precarity using propensity score matching. This aim will evaluate the impact of receiving the structural interventions which are the outcome of Aim 3 on mental health, stressors, and economic precarity. We propose to use propensity scores, but in this case where the treatment is receiving a structural intervention. Propensity scores will be developed using baseline data to predict the probability of receiving a structural intervention. We will then assess the impact of these interventions using matched samples in random effects models. Mediation will be examined using Sobel’s test to examine whether RIWP effectiveness had an indirect effect on mental health, stressors, and economic precarity through structural interventions (local/state policy changes).^108–110^ This is a secondary aim because, while important, there is not enough information to assess power a priori.

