**Power.** Power estimates were obtained using a simplified pre/post design which results in conservative estimates because it does not consider the multiple assessments. Based on preliminary analyses from similar samples^42^ we assume that the correlation over-time between the outcome at baseline and posttest will be .68. We also assume that attrition in the CBO sample will be 10% based on prior RIWP research,^40^ but we allow for attrition of 30% in the random sample of Latinx immigrants, which is an appropriate attrition expectation that has limited bias in means.^111^ Finally, based on the previous trial of RIWP, observed effect sizes for significant effects were small to moderate (ranging from Cohen’s D of .30 to .45),^42^ thus our objective was to determine the power for an effect size of .3 or more. For **Aim 1,** simulations adjusting for baseline values on the outcome estimate **power to be .91** to detect an effect size of .3. For **Aims 2 and 3**, there is not an established analytic approach to power and so we used statistical simulations (conducted in R, with analyses run using LME for the continuous outcome and GLMER for the binary outcome). These analyses assumed random effects for CBO and ICCs of .03 based on previous literature examining outcomes clustered within neighborhoods.^112–114^ For the **Aim 2** simulations, data were generated according to an ANCOVA model and appropriate type II error control was examined by running simulations with an effect size of 0. Across 1000 simulations, we estimate that power to detect an effect size of .30 is **.92**. For **Aim 3**, power was estimated for a binary outcome with probability of an individual in the comparison group receiving state level interventions of .2, and the level 2 variance was .10, which is approximately equal to an ICC of .03. We estimated power to detect an odds ratio of 2 for the effect of CBOs on receiving state level of interventions as **.82**. Last, power estimates were obtained for secondary aims using a simple ANCOVA formula in G*Power.^115,116^ For **secondary aim a,** power was **.90** for an effect size of .3, with power estimates ranging from .70 (d = .28) to .95 (d = .36). For **secondary aim b**, power was **.87**, with power estimates ranging from .70 (d = .24) to .95 (d =.33). For **secondary aim c,** estimates displayed power of **.80**, with effect size of .23, with power estimates ranging from .70 (d = .19) to .90 (d = .28). Thus, the study has strong power to detect the hypothesized effects in Aims 1 and 2, and moderate power to detect effects for Aim 3. Secondary aims also have moderate to strong power to detect effects.

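### Sobel's test in secondary aim c is markedly weaker than a percentile bootstrap when both mediation paths are weak, and should be replaced

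*Protocol*

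**What the plan says.** All of this is in the Protocol, Data Analysis/Statistical Considerations.

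- **Secondary aim c** fixes the test: "Mediation will be examined using Sobel’s test to examine whether RIWP effectiveness had an indirect effect". The indirect effect runs from RIWP through structural interventions to mental health, stressors and economic precarity.
- **The mediator is binary.** Aim c states: "This aim will evaluate the impact of receiving the structural interventions which are the outcome of Aim 3 on mental health, stressors, and economic precarity". Under Aim 3, "the outcome will be a binary indicator for whether each participant accessed the structural interventions which are implemented", and that outcome is analysed with a logit link.
- **Secondary aim a** uses another method for mediation. Bootstrapped standard errors "will be used to derive confidence intervals for these mediated effects; standard errors will be adjusted for clustering of participants within CBOs using sandwich estimators". The plan gives no reason for the difference.
- **Status and power.** Aim c is presented as preliminary, with too little information to assess power in advance. The Power paragraph nevertheless gives .80 for it at an effect size of .23. It states no power for the indirect effect.

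**The concern.** An indirect effect is the product of an a path (RIWP on receipt of a structural intervention) and a b path (receipt on the outcome). When neither coefficient is large relative to its standard error, the product is skewed and Sobel's normal reference is a poor one. The test then rejects too rarely, both under the null and when mediation is real.

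Whether RIWP works partly through access to relief policies is a natural question for a trial built around nested levels of intervention. A test that needlessly gives up power makes a missed indirect effect more likely. A second, separate issue is the scale on which the indirect effect would be reported if the a path came from the Aim 3 logit model.

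**Working it through.** **Inputs from the Protocol**
- Randomised sample: "randomly assigned to an efficacious peer advocacy and learning model (RIWP; n=150) or a treatment-as-usual waitlist control group (TAU; n=150".
- Attrition: "We also assume that attrition in the CBO sample will be 10% based on prior RIWP research", so 150 × .90 = 135 per arm.
- Baseline to post-test correlation .68, so the adjusted residual SD is √(1 − .68²) = .733.
- Receipt in the comparison group .20. An odds ratio of 2 takes this to .333.
- Effect size for aim c: d = .23. Design effect size: d = .30.

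**Assumptions**
- Two-sided alpha .05, which is not stated.
- The odds ratio of 2 and the .20 base rate are given for CBO engagement, not for RIWP. Using them for RIWP against TAU is a borrowing.
- No direct effect, clustering, matching or repeated timepoints.

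**Reproducing the plan's own figures**
- Aim 1: SE = .733 × √(2/135) = .0892; .30/.0892 = 3.36; power = Φ(3.36 − 1.96) = .919, against the stated .91. The set-up is therefore close to the plan's.
- Aim c: the stated .80 at d = .23 is matched by 300 against 300 without baseline adjustment (.804). No sample size is given for it. The three stated points (d = .19, .23, .28 at power .70, .80, .90) imply unadjusted totals of 684, 594 and 538, so no single total reproduces them. In any case these are not powers for an indirect effect.

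**Why Sobel loses, by hand (receipt .20 v .333, d = .23)**
- a path: SE = √[(.20 × .80 + .333 × .667)/135] = .0532; z_a = .1333/.0532 = 2.51; power Φ(.55) = .71.
- b path: SE = .733/√[135 × (.160 + .222)] = .1021; z_b = .23/.1021 = 2.25; power Φ(.29) = .61.
- Sobel's statistic is z_a·z_b/√(z_a² + z_b²). At the expected path values it is 2.51 × 2.25/√(2.51² + 2.25²) = 1.68, short of 1.96 although each path alone exceeds 1.96.
- Requiring both paths to be significant has power of about .71 × .61 = .43. Treating z_a and z_b as independent normals, Sobel has .21.

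**Simulation** (RIWP → binary receipt → continuous outcome, baseline-adjusted, 135 per arm, 500 bootstrap samples per trial; small ranges are between runs)

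| Receipt, TAU v RIWP | b path | Sobel | Percentile bootstrap |
| --- | --- | --- | --- |
| .20 v .333 | .23 | .20–.22 | .40–.43 |
| .20 v .333 | .30 | .35–.37 | .55–.58 |
| .333 v .50 | .23 | .32–.34 | .54 |
| .20 v .333 | .45 | .60 | .71 |
| OR 3 from .20 | .30 | .74 | .83 |
| .20 v .20 (no a path) | .30 | .005–.007 | .037–.040 |

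The last row is a null case: the percentile bootstrap does not buy its power with excess false positives. A bias-corrected bootstrap rejected .066 there, so percentile is the safer form.

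**Is the binary mediator the cause?** No. At odds ratio 2 and d = .23, Sobel with a logit a path gives .19–.20, against .21–.22 with a linear a path in the same runs.

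**Would the wording of aim a repair it?** Not if it means a normal interval from a bootstrapped standard error. That gives .19 in the same scenario, no better than Sobel.

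**Scale.** With the Aim 3 logit model as the a path, the product is ln 2 × .23 = .693 × .23 = .159. On the outcome scale the indirect effect is (.333 − .20) × .23 = .133 × .23 = .031, about a fifth of that.

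**The case against.** The strongest reply is that the Protocol supplies neither a RIWP effect on receipt nor a sample for this test, so any power figure rests on a chosen scenario. TAU participants are themselves recruited through CBOs, so on the Protocol's own odds ratio their receipt rate could be nearer .333 than .20. Aim c is exploratory, and the error is in the conservative direction. These points stand, and they limit the weight of the finding. The .333 v .50 scenario still shows a gap of about 20 percentage points.

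Readers might infer four stronger things that the documents do not support:

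- **That Sobel halves the power in general.** It does so near odds ratio 2 and d = .23 in the randomised sample. The ratio of Sobel to bootstrap power is about .64 at d = .30, .84 at d = .45, and .89 at odds ratio 3 with d = .30.
- **That the binary mediator causes the power loss.** The logit and linear a paths give almost the same Sobel power.
- **That a negative answer would be due to the test and not the data.** With bootstrap power of about .40 at d = .23, a negative answer stays more likely than not.
- **That the reported indirect effect will be uninterpretable.** The Protocol does not say how the a path is modelled in the mediation analysis or that a raw product will be reported. The scale problem is conditional on using the Aim 3 logit model.

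One counter-example does not apply. In a contrast of 270 CBO participants with 700 from the random sample ("we allow for attrition of 30% in the random sample of Latinx immigrants"), the two methods nearly coincide (.95 v .97). That is the CBO comparison. The Sobel sentence concerns RIWP, which is randomised only among CBO participants.

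**Conclusion.** The point holds in a limited form. Sobel's test is fixed for an indirect effect whose a path rests on about 270 randomised participants, and it is the weaker test there. Power is about .20 against .40 at d = .23, about .36 against .55 at d = .30, and about .34 against .54 with receipt .333 v .50 at d = .23. These figures rest on an odds ratio borrowed from the CBO comparison, an assumed alpha, and a simulation without clustering, matching or repeated measures. The loss shrinks as the paths strengthen, and the better method does not make the analysis well powered. The scale issue is separate and arises only if the Aim 3 logit coefficient enters the product. No primary aim is affected, and false-positive risk is not raised.

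**What to change.** - In secondary aim c, replace Sobel's test with a percentile (not normal-theory) bootstrap confidence interval for the indirect effect. Resample whole participants, with all their timepoints, within CBO and arm, and repeat any propensity-matching step in each resample.
- Report the indirect effect on the outcome scale: the difference in receipt probability between RIWP and TAU times the effect of receipt.
- In secondary aim a, state that the interval is a percentile interval, so that both mediation analyses use the same method.

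No new data are needed. The cost is a short text change, extra computing, and some added analysis work to build the matching step and repeated measures into the resampling. Because the simulations here include neither, the behaviour of the interval under the final model should be checked when it is programmed.

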This study is specifically designed to be sensitive to the changing impacts of the pandemic and the effectiveness of the multilevel interventions in reducing those. Thus, we propose 5 data collection points, every 8 months over 32 months. Our primary outcomes – psychological distress, daily stressors, and economic precarity – tend to be moderately stable^93–98^ but may also be impacted by shocks such as losing a job or getting COVID-19. Given the unknown trajectory of the pandemic and the path of economic recovery, we do not know a priori what the best approach to use for the longitudinal data will be. Therefore, our proposal is to use those in the random comparison sample in order to explore longitudinal models which will capture a large portion of the variability in outcomes over time while also maximizing power to find treatment effects. For example, modeling effects on mean levels of the outcomes post baseline would involve only 1 model parameter but would miss much of the nuance in the data. The comparison respondents will allow us to examine possible alternatives (linear change, piecewise change, adjustments for time-varying events including unemployment and COVID infections) in data without treatment effects. We will conduct analyses and publish a paper which examines fit of alternative longitudinal models to the data, and we will conduct additional power analyses before choosing the approach which best balances model fit and power. For the remainder of the data analysis section, we assume a relatively simple model with an intercept and linear change, while power analyses assume a simple pre-post design which will result in conservative estimates of power.

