**Aim 1.** Test the effects of the RIWP intervention to reduce adverse consequences of the COVID-19 pandemic. The principal objective of this study is to test the efficacy of the RIWP intervention for participants recruited from CBOs. Because only individuals recruited from the CBO sample are eligible to be randomized to receive the RIWP intervention or treatment as usual, analysis for this aim includes only CBO participants. To examine the effects of the RIWP intervention, we propose a linear model with random effects for individuals. As randomization happens within CBO, there is not an explicit random effect for this included, but we do propose to use sandwich estimators,^99,100^ to adjust standard errors for any unexpected impacts of this clustering. In mixed notation the model for psychological distress is:

${Distress}_{ti}= B_{00}+{B_{01}\left( RIWP \right){+B}_{02}\left( Time \right){+B}_{03}\left( Time*RIWP \right){+\boldsymbol{B}}_{\mathbf{0}\boldsymbol{N}}\left( \boldsymbol{covariates} \right)+ r_{0ij}+r_{2ij}(Time)+ e}_{ij}$

where participation in the RIWP plus CBO is indicated by a dummy code for RIWP. Because baseline data is collected before randomization, time is centered at baseline and our aim is answered by B_03_ which is the difference in slopes of levels of distress, adjusted for covariates, between those who experience RWIP+CBO intervention and those in the CBO group.

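### The Aim 1 power of .91 is for a baseline-adjusted analysis; the working Aim 1 model leaves the T1 arm difference free and has about .87 in the same pre/post design

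*Protocol*

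**What the plan says.** All of this is in the protocol, under Data Analysis/Statistical Considerations.

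- **Power paragraph.** The Aim 1 value of .91 comes from "simulations adjusting for baseline values on the outcome estimate". The design behind it is "a simplified pre/post design which results in conservative estimates because it does not consider the multiple assessments".
- **Paragraph on the choice of longitudinal model.** It makes the same claim: "power analyses assume a simple pre-post design which will result in conservative estimates of power". It presents the intercept-plus-linear-change model as a working assumption. The final form is to be explored in the random comparison sample, with further power analyses before the choice is made. The Aim 3 paragraph refers back to this process.
- **Aim 1 paragraph.** The model has a coefficient for arm (B01), one for time (B02), one for their product (B03), covariates, and a random intercept and slope. Time is zero at baseline, and baseline is stated to precede randomization. The test is fixed: "our aim is answered by B_03_ which is the difference in slopes of levels of distress, adjusted for covariates".

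**The concern.** The analysis that was powered and the analysis that is written down are not the same. In the Aim 1 model the T1 score is on the left-hand side as an outcome, so the general covariate term does not supply the baseline adjustment that the simulations used. With time zero at T1, B01 is the arm difference at T1. Randomization follows T1, so its true value is zero. Estimating it anyway gives up the precision that baseline adjustment provides.

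With only two waves, B03 with B01 free is the difference in mean change, which is less efficient than adjustment for baseline whenever the correlation is below 1. The argument that the pre/post figure is conservative because it ignores the later waves assumes that the estimator stays the same. Here it does not. At stake are the correctness of the stated power for the study's principal test and a gain in precision that needs no new data.

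**Working it through.** **Inputs from the protocol**
- Allocation: 300 randomized, 150 per arm (Objectives/Aims: "a treatment-as-usual waitlist control group (TAU; n=150").
- Attrition: "attrition in the CBO sample will be 10% based on prior RIWP research", so 150 × .90 = 135 per arm.
- Correlation: "the correlation over-time between the outcome at baseline and posttest will be .68".
- Effect: "our objective was to determine the power for an effect size of .3 or more", so d = .30 in SD units.
- Alpha is not stated in the Power paragraph. Two-sided .05 is assumed.

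Throughout, power = Φ(effect/SE − 1.96).

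**1. Reproduce the stated figure (baseline adjusted, two waves)**
- Variance factor: 1 − .68² = .5376
- SE = √(2 × .5376/135) = .0892
- .30/.0892 = 3.36, power **.92** (stated: .91)

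**2. Working model in the same design (B01 free, two waves)**
- Variance factor: 2(1 − .68) = .64
- SE = √(2 × .64/135) = .0974
- .30/.0974 = 3.08, power **.87**

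The variance ratio is .64/.5376 = 1.19. Power of .91 needs 131 completers per arm with baseline adjustment and 155 with B01 free. Simulation of both analyses gave .919 and .868.

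**3. Sensitivity to the assumptions.** With one-sided .05 the pair is .957 and .925. With no attrition (150 per arm) it is .943 and .901. That .901 is also close to .91, but only if both the stated attrition and the stated baseline adjustment are ignored. With a correlation of .60 the pair is .869 and .787.

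**4. More waves.** The covariance here is assumed: compound symmetry at .68, with an optional random-slope variance τ per wave squared. With B01 free, SE(B03) = √[(2/135) × (.32/S + τ)]. S is the sum of squared deviations of wave number: 5 for T1–T4 and 10 for T1–T5. The B01 = 0 values come from generalized least squares with the same covariance.

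| Fitted and true effect | τ | B01 free | B01 = 0 |
|---|---|---|---|
| Linear to .30 at T4, T1–T4 | 0 | .100/.0308 → .90 | .94 |
| Linear to .30 at T4, T1–T4 | .01 | .100/.0331 → .86 | .90 |
| Linear to .30 at T5, T1–T5 | 0 | .075/.0218 → .93 | .96 |
| Linear to .30 at T5, T1–T5 | .01 | .075/.0249 → .85 | .89 |

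For a sustained effect of .30 from T2 to T4, fitted as a step (post-baseline mean against T1):
- B01 free: variance factor .32 × (1 + 1/3) = .427, SE .0795, power .965.
- Adjusted for T1: variance factor (1 + 2 × .68)/3 − .68² = .324, SE .0693, power .991.

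So the price of a free B01, with the fitted shape matching the true one, is 5 points in pre/post and about 3 to 4 in these multi-wave cases under compound symmetry. Free-B01 power lies on either side of .91, depending on effect shape and slope variance.

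**The case against.** **The model is provisional.** The protocol says so and promises more power work. This stands for the form of change over time. It does not cover B01: the options named concern linear or piecewise change and time-varying events, and they are to be explored in a sample with no randomized arms. That sample cannot show whether the arms should share a T1 mean.

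**A main effect beside its interaction is standard, and B03 is unbiased.** Both are true. A reader might infer that chance imbalance at T1 biases the treatment effect. Under randomization it does not. It only adds variance, and that variance is already counted in the .87.

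**The extra waves may make up the loss.** They may: T1–T5 with linear growth and no random slope gives .93. That case omits the random slope in the written model (.85 with τ = .01). It also relies on T5, 32 months after T1, while the waitlist group receives RIWP in Months 29–35. The protocol does not settle which case applies.

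**Much larger losses can be computed.** A straight line fitted to a sustained step with B01 free gives .83 for T1–T4, .79 for T1–T5 and .78 for T1–T4 with τ = .01. A reader might take these as the cost of B01. They are not, because they mostly reflect a linear fit to an effect that is not linear. With the step fitted as a step and B01 still free, T1–T4 gives .965.

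**Conclusion.** The mismatch holds, and its size is moderate. Like for like in the pre/post design, the working Aim 1 test has power of about .87, against .91 stated and .92 recomputed for the adjusted analysis. This rests on the protocol's n, attrition, correlation and effect size, and on an assumed two-sided .05. Power stays above .80, no change in sample size follows, and the validity of the test is not in question.

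It would go too far to say that the conservative label is false. The documents give neither the covariance over waves nor the expected effect shape, and plausible choices put the multi-wave power above or below .91. The supportable statement is that .91 is not an assured lower bound for the model as written.

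**What to change.** Whichever longitudinal form is finally chosen, do one of the following for Aim 1:

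1. Keep T1 among the outcomes but constrain the arms to a common T1 mean, which means dropping B01 (constrained longitudinal data analysis).
2. Use the T1 outcome as a covariate and model only the post-baseline waves as outcomes, with the treatment contrast defined on those waves.

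In the pre/post design either choice brings the analysis into line with the one that was powered, at about .92. If B01 is kept, restate the Aim 1 pre/post power as about .87. In all cases, remove the word conservative for Aim 1 unless power is recomputed for the model actually used, with its covariance and effect shape stated.

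The cost is a change of wording and one further power run, which the protocol already foresees. No extra data are needed, and randomization after T1 justifies the constraint.
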